### Procedure and randomization

First, participating schools send an information letter and consent form to all possibly eligible adolescents and their parents. After informed consent is obtained from both the adolescent and the parent(s) of adolescents aged 12–15 (for adolescents aged 16 informed consent of a parent was not required), teachers fill out the screening measures (externalizing behavior problems and severity of autism spectrum symptoms, see screening measures). Next, information about the adolescent’s intelligence is provided by the school. If information about IQ is not available or is derived from an intelligence test administered more than 2 years ago, a short IQ test will be administered. Fig. 2 shows the trial process with a Standard Protocol Items Recommendations for Interventional Trials (SPIRIT) figure.

**Fig. 2 Fig2:**
[figure not shown]
Spirit diagram. *Note. CAU* Care as Usual

If participants meet the inclusion criteria, they are randomly assigned to either the intervention or the control condition. Randomization takes place at the individual level, by means of computer-generated random numbers. Adolescents, their parents and teachers will obviously notice the condition in which they are participating, so allocation will not be blind. Nevertheless, participants will not be aware of the fact that we examine the difference between two training sequences. Subsequently, adolescent download a questionnaire application on their smartphone and start with the weekly and daily questionnaires. First, a 3-week baseline of the weekly measure (see measures section) will be established. Moreover, adolescents fill in the first Daily Diary measure on five consecutive days. In addition, adolescents, their parents and teachers complete the baseline measures at T1, the first of three assessments. The adolescent questionnaires and tasks are administered individually at school by a trained research assistant at each assessment point. Adolescents fill out the questionnaires on a computer. Teachers fill out the questionnaires on paper. Parents are sent links to the questionnaires via email.

Participants in the intervention condition start with either the cognitive module (Think Cool) or the behavioral module (Act Cool). After 5 weeks, in which participants in the intervention condition follow five individual therapy sessions, all participants, parents and teachers complete the T2 measures. Next, there is a 3-week training break, which allows us to measure possible delayed effects. During the training break, all participants continue to fill in the weekly questionnaire and fill in the second Daily Diary measure. Subsequently, participants in the intervention condition follow the second module (Think Cool or Act Cool, depending on the first module), which also consists of five individual sessions. Eventually, the post-test measures are completed by all participants at T3. There also is a 3-week post-measure of the weekly measure, in which participants also complete the third Daily Diary measure.

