### Experimental and control condition

#### Experimental manipulation

Participants in the intervention condition will receive 11 individual 45-min sessions of the Think Cool Act Cool emotion regulation training. This is a manualized experimental training, that is designed based on components of evidence-based treatments for adolescents with externalizing behavior problems, such as Coping Power [37] and Aggression Replacement Training [38]. The training is provided at the school of the participant, by a trained clinician with a background in child psychology.

Before the actual modules, participants start with an introduction session, in which they get to know the trainer, the content of the training, and set personal goals. Next, participants first receive either the Think Cool module or the Act Cool module, followed by the other module. Both modules consist of five individual sessions. The content of the modules is displayed in Table 1.

**Table 1 Tab1:** Content of the Think Cool Act Cool emotion regulation training

Session	Session components Think Cool module	Session components Act Cool module
Introduction session	• participant and clinician get to know each other • training objectives are explained • brainstorm about words for anger • formulate personal training goals	
Session 1 / 6	• make or adjust^a^ an anger thermometer, based on situations, bodily sensations and *cognitions* • explain the *Think* Cool Chain • practice with regulation strategy ‘*think* about something fun’ (cognitive distraction) • introduce at-home assignments	• make or adjust^a^ an anger thermometer, based on situations, bodily sensations and *behaviors* • explain the *Act* Cool Chain • practice with regulation strategy ‘*do* something fun’ (behavioral distraction) • introduce at-home assignments
Session 2 / 7	• look back and discuss at-home assignments • practice regulation strategy *‘talk in your head’* (cognitive relaxation) • practice regulation strategy *‘helping thoughts’* (cognitive reappraisal) • summarize and discuss new at-home assignment	• look back and discuss at-home assignments • practice regulation strategy *deep breathing* (behavioral relaxation) • practice regulation strategy *‘time out’* (behavioral modification) • summarize and discuss new at-home assignment

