### Analyses

Data will be analyzed according to the intention-to-treat principle [63], with multiple imputation as technique to handle missing data. To answer the first research question, whether the Think Cool Act Cool emotion regulation training is effective in enhancing emotion regulation skills and decreasing externalizing behavior problems, data of T1-T3 will be analyzed with analysis of variance and/or structural equation modeling. We will examine whether different aspects of emotion regulation and multi-informant perspectives of externalizing behaviors problems can be combined into latent variables. If this is the case, these latent variables will be used, in structural equation models. Otherwise, the analyses of variance will be conducted separately for the different constructs. To examine which module (Think Cool versus Act Cool) and which sequence most effectively increases emotion regulation capacities, we will use piecewise growth curve analyses and analysis of variance. Moderation will be tested by using multi-group analyses or regression analyses, and mediation will be tested with random-intercept cross-lagged panel models and parallel-process piecewise latent growth curve modeling. The analyses and reporting of results will be carried out according to the Consolidated Standards of Reporting Trials (CONSORT) [64].

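### The T1 questionnaires, the 3-week weekly baseline and the first diary follow open randomisation, so knowledge of condition may shift the baseline of the intervention-versus-control comparison

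*Protocol article*

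**What the plan says.** All of this is in the protocol article, Method/design, Procedure and randomization, unless another section is named.

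- Before assignment, the section lists consent, teacher screening and IQ. On screening it says "teachers fill out the screening measures (externalizing behavior problems and severity of autism spectrum symptoms, see screening measures".
- Assignment follows directly on eligibility: "If participants meet the inclusion criteria, they are randomly assigned to either the intervention or the control condition".
- On blinding: "Adolescents, their parents and teachers will obviously notice the condition in which they are participating, so allocation will not be blind". The one thing kept from participants is that two sequences are being compared.
- Then: "Subsequently, adolescent download a questionnaire application on their smartphone and start with the weekly and daily questionnaires". The next sentence reads "First, a 3-week baseline of the weekly measure (see measures section) will be established", and the first Daily Diary comes after it.
- T1 is next in the running order: "In addition, adolescents, their parents and teachers complete the baseline measures at T1, the first of three assessments".
- Analyses: for the first research question, "data of T1-T3 will be analyzed with analysis of variance and/or structural equation modeling".
- Experimental manipulation: "Before the actual modules, participants start with an introduction session, in which they get to know the trainer". The article does not place this session relative to T1 or the baseline weeks.

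**The concern.** In an open trial, unblinded ratings after treatment cannot be avoided, but unblinded ratings at baseline can. Here the people who rate the outcomes (adolescent, parent, teacher) may already know the condition when they give the value from which change is counted. Disappointment in the control condition, or anticipation in the intervention condition, could then move T1 apart between two groups that randomisation had made comparable.

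The measures exposed are the DERS, FEEL-KJ, vignette measure, YSR, CBCL and T1 TRF, the weekly items during their baseline weeks, and the first mood diary. Affective reactivity and parental acceptance-rejection are also absent from the list of pre-assignment measures. These two moderators may therefore be rated with knowledge of the condition as well.

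At stake is the comparison of the intervention condition (both sequences together) with care-as-usual, which is the comparison the sample size is based on.

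**Working it through.** **Step 1: the order of events.**

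| Event | Relative to randomisation | How firmly the text fixes it |
|---|---|---|
| Consent, teacher TRF and ASV, IQ | before | explicit |
| App, weekly baseline, first diary | after | explicit: the opening word of the app sentence places it after assignment |
| T1 by adolescents, parents, teachers | after | by running order only; its linking phrase is not a time marker |
| Informants learn the condition | not stated | said only to be obvious to them; no concealment until T1 is described |
| Introduction session | before the modules | not placed relative to T1 |

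The design and SPIRIT figures are not in the text available, so they could not be checked.

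**Step 2: which values precede randomisation.** The screening TRF externalizing scale (32 items) is the same scale as the teacher-reported primary outcome, and it is completed before assignment. IQ also precedes it. No pre-assignment value is described for the DERS, FEEL-KJ, vignette measure, YSR, CBCL, weekly items, affective reactivity or parental acceptance-rejection.

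**Step 3: what a shift would do.** The article states no figure for this, so there is none to reproduce. Inputs from Sample size: 80 per condition, two-sided 0.05, d = 0.25 to 0.30. Assumptions, because the documents give neither: b, the difference between conditions at T1 caused by knowing the condition (in SD), and rho, the T1–T3 correlation, with equal SDs at both times. The article does not say whether T1 enters as a repeated measure or as a covariate, so both are shown.

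*Shift at T1 only:*
- Change contrast: bias of size b. With b = 0.10, this is 0.10 SD; 0.10/0.30 = 33% and 0.10/0.25 = 40% of the planned effect.
- T1-adjusted contrast: bias of size rho × b = 0.5 × 0.10 = 0.05 SD; 0.05/0.30 = 17% and 0.05/0.25 = 20%.

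*Shift that persists equally to T3:*
- Change contrast: b − b = 0.
- T1-adjusted contrast: b − rho × b = 0.10 − 0.05 = 0.05 SD.

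**Step 4: rejection rate with no true effect and a T1-only shift.** The change score has SD √(2(1 − rho)), which is 1 at rho = 0.5. The standard error is √(2/80) = 0.158, so b = 0.10 gives 0.10/0.158 = 0.63. The two-sided 5% test then rejects with probability P(Z > 1.96 − 0.63) + P(Z < −1.96 − 0.63) = 9.7%. For the adjusted contrast the SD is √(1 − rho²) = 0.866.

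| Assumed b | Change, rho = 0.5 | Change, rho 0.3 to 0.7 | T1-adjusted, rho = 0.5 |
|---|---|---|---|
| 0.10 | 9.7% | 8.3–12.9% | 6.5% |
| 0.20 | 24.4% | 18.8–37.2% | 11.3% |
| 0.25 | 35.3% | 26.7–53.2% | 15.0% |

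These rates show how sensitive the test is. They do not estimate what will happen in this trial.

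**The case against.** The strongest reply is that the article never says when informants are told. They may notice the condition only once training begins, and the modules start after the baseline weeks. The Discussion also already names the open design as a limitation. The first part stands as a limit: contamination is possible but not shown. It does not dispose of the point, because no withholding of the condition is described, and the Discussion does not say that baseline too is collected under the open design.

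A second reply is that an early baseline does not remove rating bias. If knowing the condition shifts T1 and T3 equally, the change score cancels it. With a baseline taken before allocation, the same bias would enter the T3 contrast in full. This is correct. But that remainder is the unavoidable open-design bias already conceded, whereas the shift at T1 is avoidable.

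Four stronger readings are tempting, and the documents do not support them:

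- *A reader might infer that no primary outcome has a pre-randomisation value, so that early leavers have nothing for imputation.* The screening TRF is such a value for the teacher outcome and exists for every randomised adolescent.
- *A reader might infer that every comparison is affected.* Both sequences belong to the intervention condition, and participants do not know that sequences are compared. Knowing the condition gives no reason for the two sequences to differ at baseline.
- *A reader might infer that IQ shares the moderators' problem.* It is obtained before assignment.
- *A reader might infer that the introduction session falls inside the baseline weeks.* The stated 19 weekly measurements do equal 3 + 5 + 3 + 5 + 3, with no week left over. But a 45-minute session needs no week of its own, and the article does not date it.

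**Conclusion.** The concern holds for the intervention-versus-control contrast. As written, the weekly baseline and first diary explicitly follow open randomisation, T1 does so by the running order, and no concealment of the condition until T1 is described. Confidence is high on the order and only moderate on contamination, because the moment of disclosure is not given.

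The size is unknown. The illustration (0.10 SD in the change contrast, 0.05 SD in a T1-adjusted one, or 17 to 40% of the planned effect) rests on an assumed shift of 0.10 SD at T1 alone and a correlation of 0.5. The direction could favour either condition. It would be wrong to conclude that the trial's result is biased. What can be said is that the described order leaves open a route to bias that could be closed cheaply.

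**What to change.** Complete T1, the 3-week weekly baseline and the first Daily Diary before randomisation, or at least before the condition is disclosed to any adolescent, parent or teacher. State that the introduction session follows the last baseline measure. If the condition is already withheld until then, one sentence saying so settles the point.

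For participants already enrolled:

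- use the screening TRF as baseline covariate for the teacher outcome, and include it in the imputation model;
- report that the other baselines, including the two moderators, followed allocation;
- add a sensitivity comparison of T3 values not conditioned on T1. A shift confined to T1 cannot enter it, but a persistent rating bias enters in full. It is also less precise: at rho = 0.5 the standard error is 0.158 SD against 0.866 × 0.158 = 0.137 SD with T1 adjustment.

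Cost: a procedural amendment with no extra assessment, and the total stays at 160 (80 per condition). Allocation is known later, which shortens the time to plan the training, although the baseline weeks already precede the modules. If randomisation itself is moved, adolescents who stop during the baseline are not randomised, so more may need to be screened to reach 160, with less dropout after randomisation in return.

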### Experimental and control condition

#### Experimental manipulation

Participants in the intervention condition will receive 11 individual 45-min sessions of the Think Cool Act Cool emotion regulation training. This is a manualized experimental training, that is designed based on components of evidence-based treatments for adolescents with externalizing behavior problems, such as Coping Power [37] and Aggression Replacement Training [38]. The training is provided at the school of the participant, by a trained clinician with a background in child psychology.

Before the actual modules, participants start with an introduction session, in which they get to know the trainer, the content of the training, and set personal goals. Next, participants first receive either the Think Cool module or the Act Cool module, followed by the other module. Both modules consist of five individual sessions. The content of the modules is displayed in Table 1.

**Table 1 Tab1:** Content of the Think Cool Act Cool emotion regulation training

Session	Session components Think Cool module	Session components Act Cool module
Introduction session	• participant and clinician get to know each other • training objectives are explained • brainstorm about words for anger • formulate personal training goals	
Session 1 / 6	• make or adjust^a^ an anger thermometer, based on situations, bodily sensations and *cognitions* • explain the *Think* Cool Chain • practice with regulation strategy ‘*think* about something fun’ (cognitive distraction) • introduce at-home assignments	• make or adjust^a^ an anger thermometer, based on situations, bodily sensations and *behaviors* • explain the *Act* Cool Chain • practice with regulation strategy ‘*do* something fun’ (behavioral distraction) • introduce at-home assignments
Session 2 / 7	• look back and discuss at-home assignments • practice regulation strategy *‘talk in your head’* (cognitive relaxation) • practice regulation strategy *‘helping thoughts’* (cognitive reappraisal) • summarize and discuss new at-home assignment	• look back and discuss at-home assignments • practice regulation strategy *deep breathing* (behavioral relaxation) • practice regulation strategy *‘time out’* (behavioral modification) • summarize and discuss new at-home assignment
Session 3 / 8	• look back and discuss at-home assignment • practice to look at a situation from multiple viewpoints • introduce *cognitive* problem solving • practice perspective taking • summarize and discuss new at-home assignment	• look back and discuss at-home assignment • practice *behavioral* problem solving skills (set a boundary, ask for help, ask for an explanation) • summarize and discuss new at-home assignment
Session 4 / 9	• look back and discuss at-home assignment • practice cognitive problem solving • summarize and discuss new at-home assignment	• look back and discuss at-home assignment • practice behavioral problem solving in difficult situations (accusations, disappointments, frustration) • summarize and discuss new at-home assignment
Session 5 / 10	• look back and discuss at-home assignment • practice complete *Think* Cool Chain	• look back and discuss at-home assignments • practice complete *Act* Cool Chain

*Note:*
^a^ During the first session of the second module, the existing thermometer is adjusted. Therefore column “cognitions / behaviors” from the thermometer that was developed in the first session of the first module, is removed and a new column is added. Besides this, the sessions are the same, irrespective of the sequence in which the modules are followed

In both modules, adolescents are instructed to make daily at-home assignments, the “anger thermometer logbook”, in which they briefly describe in which situations they became angry and what strategies they used to regulate their anger and solve the issues. The situations they describe in the logbook are used in the training sessions as practice material. If adolescents do not complete the at-home assignment, clinicians use other situations from adolescents’ lives.

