### Sample size

The sample size of this study is based on the expected difference on the primary outcome variables (emotion regulation and externalizing behavior problems) between the intervention condition (both sequences together) and the control condition. Meta-analyses demonstrated that the expected effect size (*d*) of cognitive behavioral therapy for children and adolescents with externalizing behavior problems is between 0.25 and 0.30 [5, 6]. To detect a small to medium effect (Cohen’s *d* = 0.25–0.30), with a two-sided type I error rate of 0.05, a power of 0.95, and three measurement moments, we will need between 100 and 142 participants [36]. To account for dropout, we have determined the total sample size to be 160 (80 participants in the control condition and 80 participants in the intervention condition).

Because previous research did not investigate differences between cognitive and behavioral training modules, it is not possible to estimate the expected effect size for the difference between modules. However, a sensitivity-power analyses showed that with 80 participants in the two intervention arms, an error rate of 0.05, a power of 0.95, and 19 repeated weekly measurements, even small effect sizes of 0.09 can be demonstrated with within-subjects analyses [36].

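### The sample size makes no allowance for clinician clustering in the intervention arm, and no clinician term is named for the main comparison, so the standard error would be too small if the clinician ICC is positive and ignored

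*Protocol article*

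**What the plan says.** All references are to the Protocol article.

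- **Delivery (Experimental manipulation):** trained participants have 11 individual sessions. "The training is provided at the school of the participant, by a trained clinician with a background in child psychology". The section on clinician training and supervision speaks of clinicians in the plural, but neither their number nor their caseload is stated.
- **Control condition:** care-as-usual at school, with no study clinician.
- **Allocation (Procedure and randomization):** individual, by computer-generated random numbers.
- **Sample size:** based on the difference "between the intervention condition (both sequences together) and the control condition", for effects of 0.25 to 0.30, "with a two-sided type I error rate of 0.05, a power of 0.95, and three measurement moments". The result is "we will need between 100 and 142 participants". The margin above that has one stated reason: "To account for dropout, we have determined the total sample size to be 160", which is 80 per condition. No ICC, caseload or design effect appears.
- **Analyses:** for the first research question, "data of T1-T3 will be analyzed with analysis of variance and/or structural equation modeling". Latent variables are used if they can be formed. Otherwise analyses of variance are run separately per construct. No clinician term is named.

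**The concern.** Adolescents treated by the same clinician share that clinician's skill, style and adherence, so their outcomes may be correlated. One-to-one sessions remove correlation between members of a therapy group, but not correlation due to a common therapist. Controls have no such source. Variance would then be inflated in one arm only, and a test that treats all participants as independent with a common error variance would understate the uncertainty of the difference.

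The plan itself gives some reason to expect an ICC above zero. The Hypotheses section expects better treatment integrity to go with greater effectiveness, and the Treatment integrity section measures adherence from the clinician after every session. If adherence differs between clinicians and affects outcome, clinicians contribute variance.

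At stake are the type I error and interval width of the comparison on which the sample size rests, and the stated power of 0.95.

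**Working it through.** **1. Reproducing 100 and 142.** Inputs from the Sample size section: two-sided alpha 0.05, power 0.95, three measurements, effects 0.25 and 0.30. Assumed, because not stated: correlation between measurements rho = 0.5. For the between-group test of a repeated-measures analysis of variance with two groups:

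lambda = f² × N × 3 / (1 + 2 × rho), with 1 and N − 2 degrees of freedom.

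- f = 0.25, N = 142: lambda = 0.0625 × 142 × 3 / 2 = 13.31, power 0.952.
- f = 0.30, N = 100: lambda = 0.09 × 100 × 3 / 2 = 13.50, power 0.953.

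These are the smallest even totals that reach 0.95, so both stated figures reproduce exactly. The formula has no clustering term. The match requires entering 0.25 and 0.30 as Cohen's f although the text calls them Cohen's d. That is a separate problem (see objection), and the power figures below keep the plan's own convention.

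**2. Partially nested variance.** Let J be the number of clinicians and m = (N/2)/J the caseload.

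- Design effect in the trained arm: DE = 1 + (m − 1) × ICC.
- Variance factor for the difference, equal arms: VI = (1 + DE)/2.
- True/naive standard error: √VI.
- Approximate type I error of the naive test: 2 × [1 − Φ(1.96/√VI)].

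J and ICC are not in the documents. Assumed ranges: J = 5 to 20, ICC = 0.01 to 0.10.

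**3. Effect on the test at N = 160 (80 per arm).** The simulated column is a naive two-group test with 40,000 runs per case.

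| J | ICC | m | DE | VI | True/naive SE | Type I, formula | Type I, simulated |
|---|---|---|---|---|---|---|---|
| 20 | 0.01 | 4 | 1.03 | 1.015 | 1.007 | 0.052 | 0.052 |
| 10 | 0.05 | 8 | 1.35 | 1.175 | 1.084 | 0.071 | 0.074 |
| 10 | 0.10 | 8 | 1.70 | 1.350 | 1.162 | 0.092 | 0.090 |
| 5 | 0.10 | 16 | 2.50 | 1.750 | 1.323 | 0.138 | 0.139 |

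With ICC = 0 the same simulation gave 0.051 to 0.052, so the first row cannot be told apart from no effect.

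**4. Effect on power at N = 142, 0.25 input.** Divide lambda = 13.31 by VI, recomputed with m = 71/J.

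| J | ICC | VI | lambda/VI | Power | N for 0.95 (0.25 input) | N for 0.95 (0.30 input) |
|---|---|---|---|---|---|---|
| none | 0 | 1 | 13.31 | 0.952 | 142 | 100 |
| 20 | 0.01 | 1.013 | 13.14 | 0.950 | 144 | 100 |
| 10 | 0.05 | 1.153 | 11.55 | 0.922 | 166 | 110 |
| 10 | 0.10 | 1.305 | 10.20 | 0.887 | 206 | 124 |
| 5 | 0.10 | 1.660 | 8.02 | 0.803 | 436 | 182 |

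The required N holds J fixed, so added participants enlarge caseloads. The ICC is taken to apply to the average of the three measurements. These powers keep N − 2 degrees of freedom and are therefore somewhat generous when clinicians are few.

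**The case against.** **The analysis wording is silent, not wrong.** A reader might infer that the plan commits to an analysis of variance that treats participants as independent. The text does not say so. It names analysis of variance and/or structural equation modeling, falls back on analysis of variance only if latent variables cannot be formed, and excludes no clinician term. A condensed article may leave the error structure to the full protocol or analysis plan. This stands, so the point about the standard error must be conditional. It does not cover the sample size, where the article commits to specific numbers.

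**The inputs are not in the documents.** A reader might also infer that standard errors are too small and that the test does reject too often. That needs caseloads above one and an ICC above zero, and neither is stated. Caseloads above one are a near-certain inference, since otherwise 80 trained clinicians would be needed. A positive ICC is plausible but not shown. The training is manualized and given individually, clinicians have a two-day course and at least two supervision sessions, and integrity is monitored. These features aim to reduce differences between clinicians, so low ICCs belong in the range. At ICC 0.01 with 20 clinicians the problem is negligible.

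**The power loss is modest beside another problem.** The stated 100 and 142 arise when d is entered as f. With f = d/2 the same test needs 388 (d = 0.30) to 558 (d = 0.25), and N = 160 has power of about 0.64 to 0.49. This is a larger and separate matter. It does not remove the clustering point, since any positive ICC would reduce further whatever power remains.

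**Conclusion.** The point holds conditionally. The partially nested structure follows from the text together with a near-certain inference about caseloads, and the stated sample size contains no allowance for it. If the clinician ICC is above zero and the analysis omits it, the standard error for training versus care-as-usual is too small and the power of 0.95 is overstated.

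The size depends on two quantities the article does not give. Under the assumed ranges it runs from nothing of practical note to a type I error nearly three times nominal (0.139/0.05 = 2.8). A middle case of 10 clinicians and ICC 0.05 gives a standard error 8% too low relative to the naive value (ratio 1.084), type I error of about 0.07 and power of 0.92 at N = 142. In that case the 0.25 input needs 166 participants, above the planned 160 before any dropout, while the 0.30 input needs 110 and stays within it. The documents do not support a firm statement that the trial's main test will be invalid.

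**What to change.** 1. **Link each intervention participant to the clinician.** Clinicians complete an integrity questionnaire after every session, so the link should already be recoverable. Confirm that clinician identity is kept in the analysis data.
2. **Name a partially nested mixed model for the condition effect:** clinician random effect in the intervention arm only, separate residual variances by arm, and Satterthwaite or Kenward-Roger degrees of freedom.
3. **If structural equation models are used,** apply cluster-robust errors only with a small-sample correction. With 5 to 20 clinicians, uncorrected robust errors tend to be too small.
4. **Restate the power** with the number of clinicians, the expected caseload and an ICC range that includes 0.01. Do this together with the d-versus-f correction.

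**Cost.** Little work, some precision, and a slightly lower stated power in most cases. As a guide at 80 per arm, approximate Satterthwaite degrees of freedom are (1 + DE)² / [DE²/(J − 1) + 1/79], and the interval widens by √VI × t(df)/1.975:

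- J = 20, ICC 0.01: df = 2.03² / (1.03²/19 + 1/79) ≈ 60; width 1.007 × 2.000/1.975 ≈ 1.02 times naive.
- J = 10, ICC 0.05: df = 2.35² / (1.35²/9 + 1/79) ≈ 26; width 1.084 × 2.057/1.975 ≈ 1.13 times naive.
- J = 5, ICC 0.10: df = 3.5² / (2.5²/4 + 1/79) ≈ 8; width 1.323 × 2.318/1.975 ≈ 1.55 times naive.

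The cost is slight unless clinicians are few and the ICC is high, which is also where the naive interval is most misleading.
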